### Relapse or reinfection

With symptoms of urinary irritation suddenly aggravated, and quantitative culture for bacteria in clean-catch midstream urine shows bacterial colonies ≥ 10^5^cfu/ml, that may be due to relapse (with the same strain of organism) or reinfection (with a different strain or species of organism) [1]. Importantly, it is necessary to exclude specimen contamination and gynecological inflammation.

### Statistics of recurrence

Recurrence rate of UTI of each patient during the treatment until the end of the follow-up will be calculated separately and compared at the end of the trial.

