### Trial design

We designed a multicenter, double-blind, randomized, controlled clinical trial lasting 24 weeks, including a 12-week treatment period and 12-week follow-up. This trial was designed to comply with the *Declaration of Helsinki* [16] and the *Good Clinical Practice* (GCP) [17] (Fig. 1). The additional file 3 contains the SPIRIT 2013 Checklist.

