### Sample size

The sample size will be calculated by PASS (version 15.0) and based on the effective rate of treatment. Group sample sizes of 91 in the treatment group and 91 in the control group achieve 90% power to detect a difference between the group proportions of 0.18. The proportion in the treatment group is assumed to be 0.91, and the proportion in the control group is 0.73 [18]. The significance level of the test is 0.025. With assuming attrition rate of 10%, a planned recruitment target of 200 patients will be set, 100 in each group.

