## Outcomes

### Primary efficacy outcome

The primary efficacy outcome will be the recurrence rate at the 12th week of the follow-up period.

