### Secondary efficacy outcomes

The secondary efficacy outcomes will be the post-treatment changes in renal and liver function, including serum creatinine (Scr), blood urea nitrogen (BUN), glutamic oxalacetic transaminase (GOT), and glutamic-pyruvic transaminase (GPT). Furthermore, TCM symptoms, non-infection-related physical signs, and subjective symptoms will be scored, and the number of episodes of each subject will be recorded. Meanwhile, vital signs indicators and SAEs will be monitored throughout the trial.

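### Comparing each patient's own recurrence rate distorts the reported rates when patients leave early; a count model with observed time as offset avoids this with the same data

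*Protocol article*

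**What the plan says.** The protocol article, under Statistics of recurrence, states: "Recurrence rate of UTI of each patient during the treatment until the end of the follow-up will be calculated separately and compared". It gives no denominator for these rates, no weight for time observed, and no test or model.

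Four other statements bear on this:

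- Trial design sets the planned observation time: a "clinical trial lasting 24 weeks, including a 12-week treatment period and 12-week follow-up".
- Sample size expects losses: "With assuming attrition rate of 10%, a planned recruitment target of 200 patients will be set, 100 in each group". Participant withdrawal criteria also foresees voluntary quitting and loss to follow-up.
- Data analysis puts every randomized patient in the full analysis set, so early leavers are in the comparison. It also promises multiple imputation and a sensitivity analysis, in general terms.
- Secondary efficacy outcomes says that "the number of episodes of each subject will be recorded", so the counts that an event-rate model needs are already collected.

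The primary outcome is described elsewhere: "The primary efficacy outcome will be the recurrence rate at the 12th week of the follow-up period". The sample size is built on two proportions.

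**The concern.** One rate per patient is a sound summary when everyone is observed for the same time. Here they will not be, and there are two ways to form the rate.

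- **Own observed time.** A short stay with one episode gives a very large rate, and that patient weighs as much in the mean as a patient observed for all 24 weeks. If leaving tends to follow a recurrence, the short denominators belong mainly to patients with events, and the mean is pushed up.
- **Fixed 24 weeks.** Time nobody observed is credited as free of infection. Rates are too low, and more so in the arm that loses more patients.

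What is at stake is mainly the accuracy of the reported recurrence rates and their absolute difference, and secondarily some precision. Total episodes over total observed time, which is what an offset model estimates, weights each patient by exposure and needs no further data.

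**Working it through.** **The plan's own figure.** From "The proportion in the treatment group is assumed to be 0.91, and the proportion in the control group is 0.73", with unpooled variance and one-sided 0.025:

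n = (1.960 + 1.282)² × (0.91×0.09 + 0.73×0.27) / 0.18² = 10.51 × 0.279 / 0.0324 = 90.5, so 91 per group, as stated. Allowing for attrition, 182/0.9 = 202.2, close to the planned 200. This rests on proportions and does not depend on how episode rates are compared.

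**Assumed episode rates.** The protocol gives none. Treating 1 − 0.73 and 1 − 0.91 as the chance of at least one episode in 24 weeks under a Poisson process gives means of −ln 0.73 = 0.315 (control) and −ln 0.91 = 0.094 (treatment). Linking the effective rate to recurrence in this way is an assumption.

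**Own-time denominator, single patient.** One episode, leaving at week 3: 24/3 = 8 per 24 weeks. Leaving at week 2: 24/2 = 12. A completer with one episode scores 1.

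**Own-time denominator, random dropout.** Let 10% leave uniformly over weeks 1–24. Mean time is 0.9×24 + 0.1×12.5 = 22.85 weeks, so 1/mean(T) = 0.0438. The mean of 1/T is 0.9/24 + 0.1×ln(24)/23 = 0.0375 + 0.0138 = 0.0513. The variance of the unweighted mean rate is therefore 0.0513/0.0438 = 1.17 times that of total events over total time. The rates themselves are not biased.

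**Fixed 24-week denominator.** With the same dropout, rates are multiplied by 22.85/24 = 0.952, about 5% too low; simulations gave about 4–6%. With attrition of 15% v 5%, leaving uniformly over weeks 2–24, and no true effect, one simulation gave 0.291 v 0.306: (0.306 − 0.291)/0.306 = 4.9% apparent difference.

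**Simulation.** 100 per arm, 24 weeks, two-sided 0.05, means 0.315 v 0.094, total attrition about 10%; 1,000 to 2,500 trials per setting in separate runs, whose ranges are shown. The offset model is Poisson with robust standard errors.

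| Leaving pattern (assumed) | t-test, own-time | Rank test, own-time | Offset model |
|---|---|---|---|
| Random only | 90–93% | 91–93% | 92–94.5% |
| 1 in 5 who recur leaves 2 weeks later | 78–80% | 92–93% | 93–94% |
| 1 in 5 leaves 1 week later | 71–72% | 93% | 93–94% |
| 1 in 10 leaves 2 weeks later | 83–85% | 92% | 93–94% |
| 1 in 5, 2 weeks, overdispersed (gamma shape 1) | 74% | 84–85% | 87–88.5% |

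In the second row a t-test on fixed 24-week rates had 93.9% power against 93.7% for the offset model. At a control mean of 0.6 and a rate ratio of 0.5, random 10% dropout gave 81.5% for the t-test against 85.5% for the offset model, the largest t-test loss seen under random dropout at this level.

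**Reported rates in the second row.** Own-time means were 0.40 and 0.12: 0.40/0.315 = 1.27 and 0.12/0.094 = 1.28. The absolute difference is 0.40 − 0.12 = 0.28 against a true 0.315 − 0.094 = 0.221, about 27% too large. The ratio barely moves (0.12/0.40 = 0.30; 0.094/0.315 = 0.30). The offset estimates stayed at 0.315 and 0.094, and at 0.310 and 0.094 with overdispersion.

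**Type I error.** Rejection under no effect lay between 3.1% and 5.4% for all the methods checked.

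**The case against.** The sentence names no denominator and no test, and an analysis plan that is not shown may supply both. It may even be a loose way of saying that each patient's recurrences are tallied. That stands as far as it goes: the missing test is no fault in itself. The sentence does, however, make the patient-level rate the thing compared, and a plan that followed it would inherit the problem.

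A reader might infer that the trial loses 15 to 20 points of power. The documents do not support this. Such losses need a t-test, which the protocol never mentions, and departure soon after a recurrence, which it does not describe. Recurrence is not a withdrawal criterion, and staff are assigned to keep patients in the study. A rank test on the same individual rates, or fixed denominators, closes nearly all of the gap.

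A reader might also infer that the rates are necessarily overstated. That is true only of own-time denominators with recurrence-linked leaving; fixed denominators err the other way, and by little.

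Finally, it would be too strong to say that multiple imputation cannot help. Imputing only the unobserved weeks keeps the episodes already seen and would lessen the problem. But the imputation sentence is general and not tied to unequal observation time, and an own-time rate is not a missing value, so nothing clearly triggers imputation.

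**Conclusion.** The point holds as one about the accuracy of the reported recurrence rates, with a modest cost in precision. Own-time means would be about 28% too high if one in five patients who recur leaves two weeks later; fixed 24-week rates would be about 4–6% too low at about 10% attrition. With random 10% dropout a t-test on own-time rates loses about 1–4 points of power, with no bias in the rates and type I error near its nominal level. The episode rates, the timing of dropout and its link with recurrence are assumptions, since the protocol gives only the 10%.

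It would go too far to conclude that the sample size is wrong or that a comparison of proportions is invalid. The 91 per group reproduces and neither is touched. Nor is the offset a cure for every form of informative dropout: it stayed on target here because leaving depended on episodes already observed. The change is worth making because it costs almost nothing.

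**What to change.** Replace the sentence under Statistics of recurrence with wording such as:

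> The number of UTI episodes per patient will be compared between groups by negative binomial regression (or Poisson regression with robust standard errors), with the log of each patient's observed time as offset. All episodes and all time before withdrawal count. The result will be reported as a rate ratio with 95% confidence interval. Individual rates may be listed but will not be compared.

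Keep the planned sensitivity analysis, because the offset does not cover dropout that depends on unobserved events.

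The cost is one sentence in the protocol or analysis plan. Episode counts are already recorded and observed time follows from visit dates, so no new data, visits or patients are needed. SPSS, the package the protocol names, can fit the model. The sample size and the proportion-based comparison stay as they are.

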### Semi-quantitative assessment of non-infection-related physical signs and subjective symptoms

Non-infection-related physical signs and subjective symptoms include dysuria and urgency, underbelly distension, nocturia, low back pain or weakness, self-diagnosed UTI, and costovertebral angle tenderness [22]. Such symptoms and signs will be scored according to a semi-quantitative integral method, namely, classified into non-symptoms, mild symptoms, moderate symptoms, and severe symptoms, and represented by −, +, ++, and +++, with 0, 1, 2, and 4 points, correspondingly. The evaluation will be conducted before treatment and the 12th week after separately.

### Short-term and long-term cure rate

It will be recorded as a short-term cure if present of *full recovery* (FR) 4 weeks after the end of the medication and be recorded as a long-term cure if present of FR 12 weeks after the end of the medication [21] (Table 3).

### Safety evaluation

Safety evaluation will be performed at the time of the beginning and the end of the trial, including (1) blood routine, stool routine, and stool occult blood; (2) liver and kidney function; and (3) electrocardiogram. Keep in touch with the participants to keep abreast of adverse events or emergencies. The relationship between the experimental drugs and adverse events will be assessed with five grades of “positively related, possibly related, impossible to judge, possibly unrelated, and definitely unrelated” [21], so as to judge the adverse reactions and to count the incidence of it.

### Post-trial care and compensation

We will take necessary measures to ensure the safety of the subjects during the trial. Each subject will be reimbursed for transportation expenses. Our study center will provide insurance for non-negligent harm associated with this trial. In addition, incidences judged to arise from negligence harm (including those due to major protocol violations) will not be covered by the study insurance policies.

### Management of test drugs

The test drugs used during the trial will be specially managed by qualified pharmacists in each trial center, and the experimental drugs that need special preservation (such as light avoidance, dry, etc.) will be kept according to the requirements of the protocol. The test drugs will not available to any non-clinical trial participants and are intended only for patients enrolled for this clinical trial. Dose and usage are in accordance with the protocol strictly. The remaining test drugs will be returned or destroyed as required. Record the time, quantity, recipient, and so on of the handing out and reclaiming of the test drugs and strictly follow the record and modification specifications.

## Data management and analysis

### The roles and responsibilities of committees during this study

Investigators will be responsible for performing and obtaining the consent before any conduct of the study, recruitment, and allocation of participants to their randomized group, collection of data, and completion of the case report forms (CRFs), along with follow-up of study patients in each site. The study conduct and data collection will be monitored by DMC and SC (Table 4) to ensure that the study is conducted as GCP required. All monitoring findings will be reported in a timely manner.

**Table 4 Tab4:** The roles and responsibilities of committees during this study

Committees	Composition	Roles and responsibilities
Data Monitoring Committee (DMC)	Principle investigator, research physician, administrator, statistician	• Understand the protocol of the study • Have clinical experience and relevant professional knowledge • Organize an initiating meeting, any other investigator meeting, and site visiting • Budget administration and contractual issues with individual centers • Randomization • Audit feedback forms and verify data • Advice for lead investigators • Organize central sample collection, analysis, and eventual destruction • Responsible for trial master file • Provide risk report to regulatory agency and ethics committee
Steering Committee (SC)	Monitor, lead investigator, coordinator	• Agreement of final protocol • Organize investigator training • Monitor enrolment, allocation, collection of data, and completion of CRFs • Auditing study conduct and data collected in each site • Reviewing the progress of the study and if necessary agreeing changes to the protocol and/or investigators brochure to facilitate the smooth running of the study

### Data entry and management

Data entry and administration are the responsibility of designated data administrators by the data management system (DMS). Manual double entry of data will be used to avoid the mistake of data entry. Data collected during the course of the research will be kept strictly confidential and only data managers and statisticians have access to the data until the end of the trial. Data administrators, statisticians, and researchers will be kept blinded from treatment allocation. With the provisions of GCP, data will be kept for 5 years after the trial completes.

### Data analysis

Statistical analysis data set includes intention-to-treat (ITT) and per-protocol population. ITT will be applied to the full analysis set (FAS) consisting of all randomized subjects. Subjects who have received two or more weeks of treatment will be included in the per-protocol population. Both two sets will be analyzed at the end of this study. The reasons for excluding patients from the Per-Protocol Population should be recorded clear and documented prior to breaking blindness. Statistical analysis results of the two data set will be compared and analyzed after the trial completes.

Statistical analysis includes (1) baseline data analysis, (2) effectiveness analysis, and (3) security analysis. SPSS21.0 statistical analysis software will be used for statistical analysis. Two-sided test will be used for all statistical tests, and a *P* value less than 0.05 was considered statistically significant. Multiple imputation will be applied to missing data, and sensitivity analysis will be conducted to demonstrate the robustness of the results, when the high missing data proportions occur.

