#### Participant withdrawal criteria

Participant will withdraw or be rejected for further participation if:
Voluntarily quittingPoor adherenceAny violation of the inclusion criteriaAllergic to two or more of the originally intended drugs or have other specific and intolerable adverse reactionsDrop-out or loss of follow-up during observationLater examination finds other serious diseases (serious heart and liver function damage, blood disease, etc.) or special physiological changes (pregnancy, etc.) and not fit to continue the study

The reasons for the excluded cases will be explained, and the case report form will be kept for future reference. Anyone withdrawn within two weeks after receiving treatment will not be included in the per-protocol population and analyzed as missing data.

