#### Dosage and duration (Table 1)

TLF: one package as an oral dose four times daily (15 min after three meals and 1 h before bedtime) for 12 weeks;

**Table 1 Tab1:** Interventions: administration methods and duration in the experimental and control group

Treatment	Time					
	Week 0–2	Week 3–4	Week 5–6	Week 7–8	Week 9–10	Week 11–12
**TLF**	**○**	**○**	**○**	**○**	**○**	**○**
**Placebo**	**●**	**●**	**●**	**●**	**●**	**●**

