**CLAT**						
**Levofloxacin** (0.1 g, QN, po)	**○●**			**○●**		
**Nitrofurantoin** (0.1 g, QN, po)		**○●**			**○●**	
**Cefdinir** (0.1 g, QN, po)			**○●**			**○●**

A white circle represents the treatment of the treatment group; a black circle represents the treatment of the control group

CLAT: first, levofloxacin 0.1 g taken orally once per night for 2 weeks; next, nitrofurantoin 0.1 g taken orally once per night for 2 weeks; then, cefdinir 0.1 g taken orally once per night for 2 weeks. And then repeat one turn in accordance with the medication order above, the total course of antimicrobial therapy is 12 weeks. All antibiotics are taken 15 min after dinner. For those allergic to any of the three antibiotics, trimethoprim-sulfamethoxazole (TMP 40 mg, SMZ 200 mg) one tablet per day orally or fosfomycin-trometamol (3 g, qod, po) will be used as the alternative drug.

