#### Concomitant medications

Non-antibiotic drugs or products that may affect efficacy judgments are specifically prohibited during this trial, including cranberries, lactobacillus, D-mannose, methenamine, and other herbs. Any drugs other than those used to treat rUTI must be recorded on the observation sheet, including drug name, dose, and treatment duration.

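### The per-protocol set is defined only by two of twelve weeks' treatment, so it is a minimum-exposure set that checks the ITT result only weakly

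*Protocol article*

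**What the plan says.** The protocol article sets per-protocol membership in two places, both at two weeks.

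- Data analysis: "Subjects who have received two or more weeks of treatment will be included in the per-protocol population".
- Participant withdrawal criteria: "Anyone withdrawn within two weeks after receiving treatment will not be included in the per-protocol population and analyzed as missing data".

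The comparison set is everyone randomised: "ITT will be applied to the full analysis set (FAS) consisting of all randomized subjects". Both sets are to be analysed and their results compared. Neither is named as primary. On exclusions the Data analysis section adds only this: "The reasons for excluding patients from the Per-Protocol Population should be recorded clear and documented prior to breaking blindness". It lists no such reasons.

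The treatment these patients are meant to receive is much longer than two weeks. Trial design describes a study "including a 12-week treatment period and 12-week follow-up". The herbal granules are to be taken as "one package as an oral dose four times daily (15 min after three meals and 1 h before bedtime) for 12 weeks". For the antibiotics, "the total course of antimicrobial therapy is 12 weeks", which Table 1 lays out as three drugs in two-week blocks, cycled twice.

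The protocol also names departures from the plan. The withdrawal criteria include poor adherence and breaches of the inclusion criteria. Under Concomitant medications, "Non-antibiotic drugs or products that may affect efficacy judgments are specifically prohibited during this trial", with cranberry and other herbs among the examples.

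**The concern.** A per-protocol analysis is meant to show the effect in patients who were eligible and were treated broadly as planned. As written, the rule admits a patient who stopped after the first antibiotic block, one withdrawn in week 3 for poor adherence, one found in week 3 to be ineligible, and one who used a prohibited product throughout. The label promises something that the rule does not deliver.

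What is at stake is the value of the planned comparison. If the two sets hold nearly the same patients, their results will usually agree whatever happened to adherence, and agreement then says little about the effect of the full 12-week combination. No other set in the article estimates that effect.

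**Working it through.** **1. The two rules side by side.** Data analysis includes on exposure (at least two weeks received). The withdrawal section excludes on timing (withdrawn within two weeks). Poor adherence and ineligibility appear in the withdrawal section as grounds for ending participation, but its only sentence about the analysis set refers to the first two weeks. Use of a prohibited product is not linked to any analysis set. So after week 2 no stated departure removes a patient.

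**2. Size of the threshold.** Two weeks required, 12 planned: 2/12 = 16.7%. In Table 1 that is one of six blocks, ordinarily levofloxacin only.

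**3. Overlap with ITT.** Inputs from Sample size: 200 recruited, 10% attrition, so 20 leave. The share s of those 20 who leave before week 2 is not given, so I take the whole range. I also assume that nobody else receives less than two weeks.

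Size of the two-week set = 200 − 20s. Share of it that left after week 2 = (20 − 20s)/(200 − 20s).

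| s (assumed) | Two-week set, of 200 | Left after week 2 |
|---|---|---|
| 0 | 200 | 20/200 = 10% |
| 1/6 | 196.7 | 16.7/196.7 = 8.5% |
| 1/2 | 190 | 10/190 = 5.3% |
| 1 | 180 | 0% |

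The set therefore holds 90% to 100% of the ITT patients. Some who left after week 2 may have completed treatment and been lost in follow-up. Non-adherent patients who never dropped out come on top. The last column is thus not a count of short courses.

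**4. Dilution, as an illustration only.** The plan's sizing figure comes first. With 0.91 against 0.73, 90% power and one-sided 0.025 (numerically two-sided 0.05), the unpooled formula gives

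n = (0.91 × 0.09 + 0.73 × 0.27) × (1.960 + 1.282)² / 0.18² = 0.279 × 10.51 / 0.0324 = 90.5, so 91 per arm, as stated.

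Now suppose that a fraction f of the treatment arm in the set gains nothing. The difference becomes 0.18 × (1 − f). Power is for the pooled two-sided 0.05 test, held at 91 per arm.

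| f (assumed) | Difference | Power |
|---|---|---|
| 0 | 0.180 | 0.89 |
| 10% | 0.162 | 0.80 |
| 20% | 0.144 | 0.69 |

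The fractions are not in the documents. On the stated attrition alone, the share that left after week 2 is at most 10%, so the 20% row needs further non-adherence. The 0.18 is a difference in effective rate, whereas the primary outcome is the recurrence rate at the 12th week of follow-up. The table shows a direction and does not forecast the primary result.

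**5. A check on the remedy.** An adherence threshold can remove patients because of the outcome. An acute UTI during treatment brings 7 to 14 days of therapeutic antibiotics. The article does not say whether the low-dose regimen continues meanwhile. If it were paused, one 14-day course would cost 14/84 = 17% of the low-dose schedule and two would cost 28/84 = 33%. A plain 80% rule would keep the first patient and drop the second, who has had more infections.

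**The case against.** The strongest reply is that two weeks is a minimum-exposure condition and not the whole rule. The withdrawal section lists poor adherence and ineligibility as grounds for rejection, and Data analysis expects reasons for per-protocol exclusion to be recorded before unblinding, which suggests a blind review with more to decide than exposure. An adherence cut-off and a list of major violations are commonly left to an analysis plan. This has some force: the authors may intend more than they wrote. But the text says that such patients will be included, without qualification, and the only stated exclusion is by timing. A later document that removed them would contradict this one. The defect lies in a stated rule and is not a detail left open.

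Two stronger readings are tempting, and the documents do not support them. A reader might infer that the set cannot check ITT at all. It does remove very early leavers, so it is a weak check and not an empty one. A reader might also infer that agreement will be presented as proof of robustness. The article says only that the two sets will be compared, and uses the language of robustness for the missing-data sensitivity analysis.

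It is also fair to say that the harm is limited. This is a superiority trial, the full analysis set is all randomised patients, and keeping early stoppers pulls the per-protocol estimate towards ITT. On the assumptions shown, that dilutes a supportive result. No route to a false positive in the ITT analysis has been shown.

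**Conclusion.** The point holds in this form: per-protocol membership rests on 17% of the planned course and ignores the departures that the protocol itself names. The result is a minimum-exposure set that shares about 180 to 200 of 200 patients with ITT, given the stated 10% attrition and any split of leavers around week 2. Comparing the two checks the ITT result only weakly and leaves the effect in patients treated as planned unestimated.

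Confidence is high on the literal rule and its overlap with ITT. It is low on any size of dilution, because the 0.162 and 0.144 figures rest on assumed non-benefit shares and on the effective rate. The ITT set and the sample size are unaffected. The text should be corrected before unblinding, but the point does not threaten the main analysis.

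**What to change.** - Name the analysis of all randomised patients (ITT/FAS) as primary.
- Keep the two-or-more-weeks set if wanted, relabelled as a minimum-exposure sensitivity set, and make the withdrawal section agree.
- Define per-protocol as randomised patients who met the eligibility criteria, reached an adherence threshold over the 12 weeks, and used no prohibited product. The trial team should choose the threshold. 80% is one option, but the documents give no basis for a particular figure. Fix the list before unblinding.
- State that patients with an acute UTI treated during the treatment period, whom the protocol codes NR, stay in the set as failures. Neither that treatment nor any resulting interruption of the low-dose antibiotics or missed assessment may count as non-adherence or as a missing outcome.

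The cost is wording in two sections and a smaller per-protocol set. Concomitant drugs are already recorded. Management of test drugs already provides for recording quantities handed out and reclaimed, but the team must confirm that this covers the antibiotics as well as the granules, since the section does not say so.
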